### Sensitivity analysis

Univariate sensitivity analysis is used to examine the impact of the discount rate, uncertainty surrounding the unit cost data, missing data, centre-specific variation.

### Sample size

An exploratory trial in a similar population reported 35% of gingival sites were bleeding on probing (standard deviation of 25%) [16]. The Cochrane review of periodontal instrumentation (PI) suggested that six monthly PI versus no PI reduces bleeding sites by 15% [17]. The recall interval would be expected to produce an effect lower than this given that the majority of participants in all arms will still receive PI at some time during follow up. Assuming either risk-based versus 24 m or six month versus 24 m could reduce/increase the proportion of sites bleeding by 7.5%, a study with 235 in each arm could detect such a difference with 90% power at 5% significance, and likewise detect a difference of 0.3 of the standard deviation of the OHIP-14 or any other global measure of OHRQoL. For the caries clinical outcome, assuming a standard deviation of 3.5 a study with 235 participants per arm could detect a shift in white spots lesions (from 3.3 to 4.2) at 80% power and 5% significance [18].

We can combine the two strata, without introducing bias, to estimate this comparison. We anticipate smaller effect sizes for the six month versus risk-based recall comparison than six monthly versus 24 monthly given that many of the participants in the risk-based group will be seen more frequently than 24 m. A study with 750 participants in each arm could detect a difference in bleeding scores of 4.5% at least 90% power and 5% significance level, and likewise detect a difference of 0.17 of the standard deviation of the OHIP-14. For the caries clinical outcome, assuming a standard deviation of 3.5 a study with 750 participants per arm could detect a 20% relative shift in white spot lesions from 3.3 to 3.9 at 90% power and 5% significance [18].

Although there is no reason to be concerned about contamination effects in this trial or clustering by dentist, the sample size has been conservatively estimated such that if contamination occurred with 15% of the control participants or the intra cluster correlation was 0.03, the study would still have 80% power to detect the hypothesised changes in the bleeding score. Our sample size calculations indicate we need to randomise 705 participants to stratum 1 (235 in each arm) and 1030 to stratum 2 (515 in each arm).

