**Methods:**

This is a four year multi-centre, parallel-group, randomised controlled trial with blinded outcome assessment based in dental primary care in the UK. Practitioners will recruit 2372 dentate adult patients. Patient participants will be randomised to one of three groups: fixed-period six month recall, risk-based recall, or fixed-period twenty-four month recall. Outcome data will be assessed through clinical examination, patient questionnaires and NHS databases. The primary outcomes measure gingival inflammation/bleeding on probing and oral health-related quality of life.

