### Likely rate of loss to follow-up

In the power calculation we have assumed a loss to follow-up for dentists of 10% based on the observed rates of 12 and 9% in two recent large, multi-centre practice based RCTs [19]. For patient participants it is anticipated that loss to follow-up will be not more than 15% at 4 years. This estimate is based on a practice based trial conducted in North-West England where 79% of 4211 participants were retained for a period of 5 years [20]. In a recent trial conducted in a similar population 78% of participants returned a follow-up postal questionnaire. In this trial we anticipate a lower loss to follow-up because we will be using a more intensive reminder system and will explore the use of evidence based strategies to improve response.

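### The Sample size section gives 1735 (705 + 1030) as the number to randomise, but stratum 1's 235 per arm has no allowance for loss, which conflicts with the stated loss rates and with the 2372 in the abstract.

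*Protocol article*

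**What the plan says.** Four places in the protocol article bear on this.

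- **Sample size.** For the comparisons with 24-month recall, "a study with 235 in each arm could detect such a difference with 90% power at 5% significance", the difference being 7.5 points with an SD of 25. The same 235 is said to cover 0.3 SD of OHIP-14. For six-month versus risk-based recall, 750 per arm pooled over both strata is said to give at least 90% power for 4.5 points, and likewise to cover 0.17 SD of OHIP-14. The section closes with the target: "Our sample size calculations indicate we need to randomise 705 participants to stratum 1 (235 in each arm) and 1030 to stratum 2". The second stratum is to have two arms of 515.
- **Likely rate of loss to follow-up.** The 10% loss of dentists is said to have been assumed in the power calculation. For patients, the text reads: "For patient participants it is anticipated that loss to follow-up will be not more than 15% at 4 years".
- **Abstract, Methods.** "Practitioners will recruit 2372 dentate adult patients".
- **Outcome measures** (text following the list of economic outcomes). The study is said to be powered at 80% for the two primary outcomes.

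The article neither derives 2372 nor relates it to 1735, and gives no stratum split for it.

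**The concern.** The per-arm numbers in the power statements are the ones multiplied up into the randomisation target: 3 × 235 = 705, 2 × 515 = 1030, and 235 + 515 = 750. If 235 already meets 90% power exactly with complete data, then either loss was not in the calculation, contrary to the next section, or 705 and 1030 are analysed numbers and the word randomise is wrong.

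This matters most for stratum 1. Only that stratum has a 24-month arm, so the 24-month contrasts rest on it alone, and 705 is the only stratum 1 target in the document. A team working to 705 would reach its printed target and still miss the stated power on the 24-month question.

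**Working it through.** **Inputs (Sample size section).** SD 25 points; differences 7.5 points (d = 0.30) and 4.5 points (d = 0.18); OHIP-14 d = 0.17 for the pooled comparison; 5% significance, taken as two-sided because the article does not say; equal allocation. **Loss (next section).** 10% dentists, up to 15% patients.

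**Step 1: reproduce the plan's figures with no loss.** n per arm = 2(1.960 + 1.282)² / d² for 90% power.

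- d = 0.30: 234 needed; 235 gives 90.2%. No room for loss.
- d = 0.18: 649 needed; 750 gives 93.6%. Some slack.
- d = 0.17: 728 needed; 750 gives 90.9%. Little slack.

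**Step 2: power if 1735 are randomised as written.** Analysed n per arm = n × (1 − loss); power = Φ(d√(n/2) − 1.960). The documents do not say how the two loss rates combine, so a range is shown. The 23.5% assumes that they multiply: 1 − 0.90 × 0.85.

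| Comparison | Stated | 10% loss | 15% loss | 23.5% loss | 25% loss (added) |
|---|---|---|---|---|---|
| 24-month contrasts, 7.5 points | 90% | 87.0% (n = 212) | 85.0% (n = 200) | 81.2% (n = 180) | 80.4% (n = 176) |
| Six-month v risk-based, 4.5 points | at least 90% | 91.1% (n = 675) | 89.5% (n = 638) | 86.2% (n = 574) | 85.5% (n = 563) |
| Six-month v risk-based, OHIP-14 0.17 SD | at least 90% (read from the word likewise) | 87.8% | 85.9% | 82.1% | 81.4% |

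The 0.30 SD OHIP-14 figures for the 24-month contrasts equal those in the first row. Contamination and clustering are left out throughout.

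**Step 3: number to randomise so that 705 and 1030 are analysed.** N / (1 − loss), rounded up.

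| Loss | Stratum 1 | Stratum 2 | Total |
|---|---|---|---|
| 15% (patients only) | 830 | 1212 | 2042 |
| 23.5% (multiplied) | 922 | 1347 | 2268 (2269 if each stratum is rounded up) |
| 25% (added) | 940 | 1374 | 2314 |

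None of these totals equals 2372, which corresponds to a loss of 1 − 1735/2372 = 26.9%. All lie below it.

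**The case against.** The strongest reply is that the trial plans to recruit 2372, not 1735, so the shortfall never arises. Split in the 705:1030 proportion, 2372 gives about 964 in stratum 1 (2372 × 705/1735). After 23.5% loss that leaves about 246 per arm in stratum 1 and about 784 per arm pooled, both above 235 and 750. This stands. A reader might infer that the trial is underpowered, but the document does not support that: 2372 is most likely the loss-inflated target and 1735 the number needed with outcome data.

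Other parts of the reply also stand.

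- Only the dentist loss is said to be in the power calculation; the patient loss is merely anticipated. The 15% may already include patients lost with their dentist, so 23.5% is one assumption among several. Even so, 10% alone takes the 24-month contrasts to 87%.
- The 750 per arm is not loss-free for bleeding: 649 suffice.
- The 80% claim under Outcome measures survives the stated losses at 5%.
- The Statistical analyses section sets a 2.5% level, at which power would be lower. That is a separate inconsistency and is not counted here.
- A condensed article may leave the derivation and split of 2372 to the full protocol, and the monitoring committee is already to review progress and divergences from the design.

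It could also be said that recruited differs from randomised, because consent precedes the suitability examination. But patients judged unsuitable for 24-month recall enter stratum 2 and are still randomised, and no attrition at that step is stated.

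What the reply does not remove is that the article prints analysed numbers as the numbers to randomise.

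**Conclusion.** The point holds as an error in a stated sample size, not as proof of inadequate power. The randomisation figure of 1735 cannot stand beside the loss rates and the 2372. Randomising 1735 as written would give about 85% (15% loss) to 81% (23.5% loss) for the 24-month contrasts against the stated 90%. For six-month versus risk-based recall it would give 89.5% to 86% on bleeding, against at least 90%, and 86% to 82% for 0.17 SD of OHIP-14.

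These figures assume a two-sided 5% test, the normal approximation and no contamination or clustering; the lower ends also assume that the two loss rates multiply. That 2372 is the inflated target is the likely reading, but the article does not say so, and its loss rates do not reproduce that number.

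**What to change.** In the Sample size section, restate 705 and 1030 as the numbers needed with four-year outcome data. Then give the number to randomise in each stratum, the loss rate used and how dentist and patient loss were combined, and reconcile the total to 2372. The choice of loss rate is the sponsor's; the totals of about 2042, 2268 and 2314 show the range, not a prescribed value. State the stratum 1 target separately, so that reaching the overall total cannot hide a shortfall in the stratum that carries the 24-month contrasts.

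The cost is a few restated figures. Each of these totals lies within 2372, so no extra participants and no change of design are needed.

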### Likely rate of loss to follow-up

In the power calculation we have assumed a loss to follow-up for dentists of 10% based on the observed rates of 12 and 9% in two recent large, multi-centre practice based RCTs [19]. For patient participants it is anticipated that loss to follow-up will be not more than 15% at 4 years. This estimate is based on a practice based trial conducted in North-West England where 79% of 4211 participants were retained for a period of 5 years [20]. In a recent trial conducted in a similar population 78% of participants returned a follow-up postal questionnaire. In this trial we anticipate a lower loss to follow-up because we will be using a more intensive reminder system and will explore the use of evidence based strategies to improve response.

### Ethical considerations

The trial will be coordinated by TOD in the University of Dundee and CHaRT in the University of Aberdeen – both centres with experience of multicentre trials, cognisant of the implications of research governance and other legal frameworks for the conduct of trials. Informed signed consent will be obtained from the trial participants who will be given sufficient time to accept or decline involvement and are free to withdraw from the study at any time. The design of the study ensures that adults for whom a 24-month recall interval may be detrimental are not put at risk of allocation to this group. It will be made clear to participants and dentists that participants may attend at any time if there is a need for a dental appointment between recall visits. No dental treatment including referral to specialist services will be withheld from participants as a result of taking part in the trial.

This is not classed as a trial of any investigational medicinal products or procedures, and so does not come under EU Clinical Trials Directive. We will continue to conduct the study to the standards required by the NHS Universities Research Governance Framework as well as all other applicable legal, ethical and regulatory requirements.

### Data protection and archiving

Participants will be reassured that all data which are collected during the course of the research will be kept strictly confidential. All participants’ details will be anonymised and stored on a database under the guidelines of the 1998 Data Protection Act. The relevant research documentation will be archived at the University of Dundee for at least five years after completion of the trial as required by the applicable regulatory requirement(s).

### Governance arrangements

Research Governance applies to everyone working in the TOD and CHaRT. All research will therefore be conducted within the appropriate legislative and regulatory environment and in accordance with Good Clinical Practice (GCP). All staff involved in the trial at the two centres will have undertaken appropriate GCP training. The two main groupings that contribute to the governance arrangements for this study are: an independent Trial Steering Committee (TSC); and an independent Data Monitoring Committee (DMC). The TSC includes an independent Chairperson and other independent members including a consumer representative/lay person. The TSC will also comprise a selection of the co-applicants including the joint Chief Investigators ([name] and [name]), and the trial statistician ([name]). There will only be two voting members drawn from any of the co-applicants. The TSC will meet annually throughout the course of the study. The Data Monitoring and Ethics Committee will continue to report any recommendations to the Chair of the TSC, meeting before the TSC. The Trial Management Committee (TMC) will include all co-investigators and act in an advisory capacity.

The University of Dundee has agreed to act as sponsor. As such, the TOD will undertake to communicate promptly and effectively with the sponsor to satisfy the sponsor’s obligations on the authorisations, financing and progress reporting of the trial are met.

### Arrangements for day to day management of the trial

The trial will be co-ordinated from the TOD and will provide day to day support for the dental practices. CHaRT will provide the database applications and IT programming for the TOD, host the randomisation system and take responsibility for all statistical aspects of the trial. The TOD will be responsible for transacting the randomisation, collecting all trial data, co-ordination of patient participant follow-up appointments, and data processing. The dental practice will be responsible for recruiting participants (including initiating the randomisation call). An Operations Management Committee, led by the Trial Manager, will meet weekly in the early stages at the TOD to ensure smooth running of the trial, trouble-shooting issues as they arise and ensuring consistency of action across the participating centres. CHaRT staff will join this group as required, weekly by teleconference and in person every 4–6 weeks. These face to face meetings will become less frequent as the trial progresses successfully, and increase again in frequency as the trial enters its closedown phase. The TMC will meet annually and be chaired by the Chief Investigators and include all the co-investigators and key members of the TOD and CHaRT. Their remit will be to oversee the progress of the trial in an advisory capacity.

### Publication

The results of the study will be reported first to study collaborators. A main report will be drafted by the project management group and circulated to all clinical co-ordinators for comment before a final version is considered for publication by the TSC.

### Dissemination

The results of this trial will be disseminated widely and actively through professional, primary care, public and scientific routes. Results will be communicated directly to all participating dental practices and an open workshop will be held with them discussing the next steps in getting the findings of the study to influence clinical practice. The trial results will be used to inform policy (through targeted feedback to all of the UK Health Departments and the British Association for the Study of Community Dentistry and its Consultants in Dental Public Health Group); practice (through specific communications to NICE, the British Dental Association and the Faculty of General Dental Practice (UK)); the public (through INVOLVE and patient organisations) as well as with dental education and training through a range of communications to postgraduate dental Deans and the undergraduate dental schools.

Given the current dearth of directly applicable evidence around this important research question it is anticipated that the impact of this trial will be felt at the International level as well as closer to home (specific presentations will be made to the International Association for Dental Research and its Evidence Based Dentistry Network as well as to organisations such as the European Association for Dental Public Health and related European specialty societies for research and practice).

## Discussion

The INTERVAL Dental Recalls Trial is an NIHR HTA funded trial being undertaken across the UK and will begin to address the lack of high quality evidence to aide dental practitioners, patients and policy makers in their decision making regarding allocation of dental recall intervals.

In order to ensure the results of this trial are widely applicable, the geographical areas that are included in the INTERVAL Trial have been selected to yield a cross-section of practices, operating in a range of different environments and circumstances (e.g. high, middle or low income communities, fluoridation status, rural and urban, method of remuneration of GDPs (capitation and fee for item of service or a banded payment system based on Units of Dental Activity (UDA)).

The study team is multidisciplinary and broad-based, which will ensure that whilst the trial design and conduct is of the highest standard, it remains practical and pragmatic at all times. We expect the INTERVAL Trial to provide evidence that will benefit the future dental care, improve outcomes of treatment and inform decision making by policy makers, clinicians and patients, within and out with the UK National Health Service.

## Abbreviations

BSA: Business services authority
CCG: Clinical commissioning groups
CEAC: Cost-effectiveness acceptability curves
CHaRT: Centre for healthcare randomised trials
CLRN: Comprehensive local research network
DCE: Discrete choice experiment
DMEC: Data monitoring and ethics committee
FT: Filled teeth
GCP: Good clinical practice
HSCBSO: Health and social care business services organisation
ICDAS: International caries detection and assessment system
ISD: Information services division
NHS: National health service
NICE: National institute for health and care excellence
NIHB: Non-insured health benefits
NIHR: National institute for health research
OHIP-14: Oral health impact profile-14
OHRQoL: Oral health-related quality of life
PI: Periodontal instrumentation
QALYs: Quality adjusted life years
RCT: Randomised control trial
SPCRN: Scottish primary care research network
TMC: Trial management committee
TOD: Trial Office Dundee
TSC: Trial steering committee
WTP: Willingness to pay
